#### Reliable Change in Generalization Measures

We will explore individual changes in generalization measures of trait self-control and cognitive control by comparing the means of pre- and postintervention scores obtained during baseline, end of intervention phase C, and follow-up.

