### Study Design

This study will be conducted using a series of 2 single-case experimental designs (SCEDs): a concurrent multiple-baseline design across participants (SCED I) [34,35] and an introduction/withdrawal design (SCED II). SCED is a family of high-quality experimental designs that can be used to draw causal inferences about the relationship between the intervention and the outcome [36,37]. In an SCED, the intervention is systematically manipulated across multiple phases of introduction and withdrawal while the outcome variable is measured repeatedly and frequently [36-38]. In this way, individual patients function as their own controls. An overview of both experiments according to the SCRIBE (Single-Case Reporting Guideline in Behavioral Interventions) guidelines [39] is provided in Table 1.

**Table 1 table1:** Single-Case Reporting Guideline in Behavioral Interventions design elements of single-case experimental designs (SCEDs) I and II.

	SCED I	SCED II
Design	Multiple baselines across participants	Introduction-withdrawal
Duration	52 days	Approximately 42 days (28-70 days)
Sequence of phases	A-B-C+follow-up	B-C-B-C
Description of phases	Phase A—baseline: 5 days minimum; no intervention, only monitoring of physical activity and self-control Phase B—Google Fit: 7 days minimum; only Google Fit intervention is administered Phase C—Google Fit+SCT^a^: 28 days minimum; Google Fit and SCT intervention are administered simultaneously Follow-up: 3 days minimum; no intervention, only monitoring of physical activity and self-control	Phase B—Google Fit: 7 days; only Google Fit intervention is administered Phase C—Google Fit+SCT: 7-28 days minimum; optimal phase length is determined from findings of SCED I; Google Fit and SCT intervention are administered simultaneously
Main outcomes	Average TACs^b^ per hour, measured continuously throughout the trial (at least 5 measures per phase) Daily self-control, measured twice daily throughout the trial (at least 5 measures per phase)	Average TACs per hour, measured continuously throughout the trial (at least 5 measures per phase) Daily self-control, measured twice daily throughout the trial (at least 5 measures per phase)
Randomization	Baseline duration is randomized with restriction to have at least 5 baseline observation days and 3 measurements	Not randomized

^a^SCT: self-control training.

^b^TAC: total activity count.

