There are several reasons for using SCED to evaluate interventions in people with SMI. First, SCEDs require only a small number of participants—typically 3 to 6. This makes it more feasible to recruit a sufficient number of participants and requires less time and financial resources from both staff and patients. Furthermore, SCEDs can handle heterogeneous samples as participants function as their own controls. This makes it possible to involve the diverse population with SMI, who may present with comorbidities and a broad range of psychosocial problems. Finally, SCEDs enable research into the working mechanisms of SCT, which is required [25] but nearly impossible to achieve through a randomized controlled trial (RCT) as an intervention is treated as a coherent whole, making it hard to open the black box of the studied intervention [40]. Overall, this makes SCEDs very suitable for the evaluation of interventions [41,42] and an excellent and feasible alternative to classic experimental designs such as the RCT.

In total, 2 SCED experiments are used to address different aspects of the overall research aim. SCED I is used to (1) determine the initial effectiveness of the intervention, (2) explore for which patients SCT may be most effective, and (3) determine how long SCT should be offered for optimal effects. The design of SCED I is A-B-C+follow-up, where A refers to the baseline phase, B is the physical activity intervention alone (Google Fit), and C is the combination of physical activity intervention+SCT intervention, followed by a follow-up in which patients are monitored but no interventions are administered. In addition, SCED I uses a mixed methods design incorporating qualitative interviews to provide insights into patients’ experiences with both the mobile SCT app and the participation in an extensive longitudinal study. To explore the onset and duration of SCT effects on self-control, SCT is offered for 4 weeks instead of the customary 2 weeks [43]. This information will be used to determine whether SCT should be offered 1, 2, 3, or 4 weeks in SCED II.

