### Randomization and Blinding

We will randomly assign participants to different baseline, intervention phase B, and follow-up durations in SCED I. All are drawn a priori using the web-based random number generator Research Randomizer [45] with the restriction of having at least 5, 7, and 28 baseline observation days, respectively. In SCED II, phase length will not be randomized as the optimal intervention length will be derived from SCED I. Phase order will not be randomized in both experiments as we are interested in the additive effect of SCT over Google Fit only.

Owing to the nature of the intervention, in which apps are used by participants, it is not possible to blind participants to the phase. The researchers responsible for supporting participants in transferring between phases will not be blinded to the phase for the same reason. Where possible, researchers only involved in data entry, processing, and analysis will be blinded to the phase to improve the reliability of the findings [36].

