#### Trait Self-control and Cognitive Control

Generalization measures assess the intervention effect on untrained tasks and are important to establish the external validity in SCEDs [36]. The SCRIBE guidelines [37] recommend that generalization measures are taken repeatedly, although not as frequently as the main outcome measures. In this study, trait self-control and cognitive control are used as generalization measures and assessed every 5 days (at least once per phase). This combination of measures is used as self-control is a multifaceted construct and it is recommended to use more than one type of measurement instrument to assess it [66].

Trait self-control is measured using the Brief Self-Control Scale (BSCS). The BSCS is a validated, brief, and psychometrically sound measure of individual differences in self-control that consists of 13 items [19,66,67]. The BSCS measures several aspects of trait self-control, including inhibitory and initiatory control [68]. Participants rate the extent to which a statement, for example, “I am good at resisting temptation,” matches them on a 5-point Likert scale ranging from 1 (*not at all*) to 5 (*very much*). A total score for self-control will be created by taking the sum of all items after recoding negatively phrased items (Cronbach α=.83-.85 [69]). Higher scores indicate higher levels of self-control, which has a medium effect on behavioral outcomes, showing criterion validity [70].

Cognitive control will be measured using the go/no-go task. This is a well-studied measure of cognitive control and has been used in previous research to assess self-control [32]. In the go/no-go task, participants are instructed to respond to target stimuli but must refrain from responding to nontarget stimuli, which requires suppressing a behavioral response. In this study, we will use average reaction time as the main parameter of cognitive control, with shorter reaction times reflecting more self-control [32,71].

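### In SCED I the planned comparison for trait self-control and go/no-go leaves out phase B, so SCT's contribution cannot be separated from Google Fit's

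*Protocol article*

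**What the plan says.** The Protocol article, Reliable Change in Generalization Measures, names the time points to be used for trait self-control (BSCS) and cognitive control (go/no-go reaction time). Individual change is explored by "comparing the means of pre- and postintervention scores obtained during baseline, end of intervention phase C, and follow-up". Phase B is not among them.

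The section Trait Self-control and Cognitive Control says that both measures are "assessed every 5 days (at least once per phase"), so each participant should have phase B scores. It gives their purpose as follows: "Generalization measures assess the intervention effect on untrained tasks".

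In Study Design, Table 1 describes phase A of SCED I as "5 days minimum; no intervention, only monitoring of physical activity and self-control" and phase B as "7 days minimum; only Google Fit intervention is administered". The text adds that "B is the physical activity intervention alone (Google Fit), and C is the combination of physical activity intervention+SCT intervention". Randomization and Blinding explains the fixed phase order by saying that "we are interested in the additive effect of SCT over Google Fit only".

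**The concern.** The question named in Randomization and Blinding, and in the Abstract's objective for both physical activity and self-control, is what SCT adds once Google Fit is in use. Phase B is the comparator for that question. Visual Analysis follows this logic for physical activity and daily self-control in SCED I, with A versus B, B versus C and A versus C. The generalization measures get only the untreated baseline, the end of the combined phase and follow-up, and no reason is given for the difference.

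A rise in BSCS score or a faster go/no-go response from A to end of C would then be uninterpretable as to its source. The article itself describes Google Fit as working through reflective self-control processes, so a Google Fit contribution to a self-control score cannot be excluded in advance. What is at stake is whether these measures can say anything about SCT in particular, when the scores needed for that are already being collected.

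**Working it through.** The plan gives no figure for this analysis (no sample size, alpha or effect size), so there is none to reproduce. Two checks follow.

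**1. What the named time points can identify in SCED I**

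Assume additive effects: g for Google Fit, s for the SCT increment, and d for drift and task practice since phase A. Assume also that the Google Fit effect present in phase B carries unchanged into phase C. At follow-up let fractions p and q of g and s persist, because Procedure has every app except the survey platform disabled.

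- End of C minus A = g + s + d(C)
- Follow-up minus A = p·g + q·s + d(F)
- Follow-up minus end of C = −(1−p)·g − (1−q)·s + d(F) − d(C)
- End of C minus B (not planned) = s + d(C) − d(B)

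Every planned contrast contains both g and s. Only the last one removes g.

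Illustration with an assumed total change of 0.5 units and no drift:

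| g | s | A to end of C | B to end of C | Google Fit share of A to C |
|---|---|---|---|---|
| 0 | 0.5 | 0.5 | 0.5 | 0% |
| 0.25 | 0.25 | 0.5 | 0.25 | 50% |
| 0.5 | 0 | 0.5 | 0 | 100% |

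The planned contrast gives the same value in all three rows.

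**2. Whether phase B scores will be there, and how many**

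Inputs from Study Design, Table 1: A at least 5 days, B at least 7, C 28 (taken at its minimum), follow-up at least 3, total 52. The minima sum to 5 + 7 + 28 + 3 = 43 days, leaving 52 − 43 = 9 days to distribute, so B could last up to 7 + 9 = 16 days.

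- A 7-day phase on a 5-day schedule holds floor(7/5) = 1 to ceil(7/5) = 2 scores.
- A 16-day phase holds floor(16/5) = 3 to ceil(16/5) = 4.
- Counting over all allowed phase lengths and start days gives 1 to 4 scores in phase B, and never none.
- A 5-day phase A holds exactly 5/5 = 1 scheduled score, apart from any questionnaire completed at the set-up visit. At minimum lengths, phase B is therefore no thinner on the schedule than the baseline the plan already uses.

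**3. What the added contrast does not remove**

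From the end of A to the end of C is at least 7 + 28 = 35 days. From the end of B to the end of C is 28 days. With a 7-day phase B, 28/35 = 80% of the elapsed time stays in the contrast, along with the repeated testing in phase C (floor(28/5) = 5 to ceil(28/5) = 6 scheduled assessments).

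**4. Whether another planned analysis fills the gap**

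Visual Analysis covers physical activity and state self-control. Piecewise Linear Regression Analysis mentions trait self-control and cognitive control only as possible moderators. Neither sets out a B versus C contrast on these two measures.

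**The case against.** A reader might infer that the plan will report a Google Fit effect as generalization of SCT. The text does not say so. The section promises only to explore individual change, and the purpose statement speaks of the intervention's effect without naming SCT. The supported statement is that the two contributions cannot be separated.

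Four further points have weight.

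- Study Objectives words the secondary objective as the effect of the combined intervention on self-control, and A versus end of C answers that. This stands as a reason to keep the contrast. It does not justify omitting B versus C, since the Abstract and Randomization and Blinding ask for the added effect.
- SCT's added effect on self-control is examined elsewhere, on the daily state measure with B versus C. This stands, and it limits the consequence to sparse, exploratory measures with no test or decision attached.
- Nothing in the documents predicts that a week or so of Google Fit would move a trait score or a reaction time. The introduction links goal setting to intentions and SCT to general self-control capacity. This also stands: the size of any Google Fit component is unknown and could be nil.
- B versus end of C does not fully isolate SCT, because time and practice remain. This stands as a limit on interpretation. The contrast still removes the Google Fit onset, which no planned contrast does.

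The point does not carry over unchanged to SCED II, which runs B-C-B-C without an untreated phase or follow-up. Study Design speaks of at least one baseline phase in both experiments, so baseline there could mean the first B phase, but the analysis section does not say so.

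**Conclusion.** The point holds for SCED I in a limited form. From baseline, end of phase C and follow-up alone, SCT's contribution to trait self-control and go/no-go performance cannot be separated from Google Fit's, although the phase B scores needed to do so are scheduled. With no effect sizes given, Google Fit's share of an A-to-C change is bounded only by 0% and 100%, if both effects are non-negative and drift is ignored. The conclusion rests on baseline meaning phase A in SCED I, which Table 1 and the contrast labels in Visual Analysis both support.

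This is an inexpensive improvement to an exploratory analysis. It does not touch the primary or secondary outcome. For SCED II the comparison as written does not fit the phase sequence and needs its own wording.

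**What to change.** In Reliable Change in Generalization Measures, state the contrasts by experiment.

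- **SCED I:** all available phase B scores versus end of phase C, as the contrast for what SCT adds; A versus B, as the change with Google Fit; A versus end of C, labelled as the combined change and tied to the secondary objective in Study Objectives. Describe follow-up as the period after both apps are removed.
- **SCED II:** B versus C.
- **Both:** keep the results descriptive and exploratory, and say that time and task-practice effects remain in the B versus C contrast.

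It would also help to reconcile the Abstract's objective with Study Objectives on whether the self-control question concerns the added or the combined effect.

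The cost is a few sentences and no new data. The added contrast will be imprecise, since phase B may hold only 1 or 2 scores if it lasts the 7-day minimum.

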#### Qualitative Analysis of Experience

Interview data will be analyzed inductively using thematic analysis [79] to organize data into overarching themes related to usability and feasibility of the SCIPP app and SCED methodology according to people with SMI.

## Results

Funding for this study was obtained in July 2020 by The Netherlands Organisation for Health Research and Development (project 555003023). It was approved by the Ethics Committee/domain Humanities and Social Sciences of the Faculty of Behavioural, Management, and Social Sciences at the University of Twente in November 2021 and the research committees of the participating mental health care facilities in January 2022. Recruitment for the study started in January 2022, and 6 participants have been included as of March 2023. We expect to publish the results in summer 2023.

## Discussion

### Expected Findings

Earlier studies have shown that SCT using the nondominant hand paradigm can increase self-control in healthy populations [24-26]. Self-control is a key mechanism in translating physical activity intentions into practice [80,81]. Therefore, interventions targeting self-control may be a viable strategy for improving physical activity in people with SMI. Many people with SMI experience poor physical health yet are barely targeted in preventive and health promotion research, leading to large systemic inequality [82]. In addition, people with SMI face a number of social, cognitive, physical, psychological, and sensory impairments, which may make cognitively based physical activity interventions less accessible [83,84]. However, further studies are needed to evaluate the effect of combining SCT and regular physical activity interventions on physical activity in this target group. This study will provide initial insights into whether this is the case.

SCIPP, the SCT app that will be used in this study, is expected to be feasible, effective, and suitable for people with SMI. First, it brings SCT to the digital era as it is delivered via a mobile app. Among other things, an app can be used by patients individually, on their own time, and at their own pace; is scalable; and can increase patient motivation and adherence, making it a suitable instrument to target people with SMI [85]. Previous research has indeed shown that there is a need for well-designed mobile apps to further improve treatment of hard-to-involve patient populations [86]. Second, based on earlier research on SCT and a specific study on an SCT app, it is expected that SCIPP will be effective. We have previously developed and pilot-tested a functioning prototype of an SCT app aimed at students and found that self-control increased after just 10 days [32]. Even though this was studied in a different target group, it still shows the potential of this app to bolster self-control as it is expected that the underlying mechanisms of self-control practice are similar across populations. The findings of this previous study were used to further develop the SCT app, resulting in SCIPP. This study especially highlighted the importance of reminders to ensure that participants did not forget about the SCT tasks throughout their day. Second, SCIPP was specifically designed with and for this target group following a participatory design process in which patients were structurally involved in app development via 3 design workshops. Products designed through a participatory design approach often have a better user experience and usability as they fit more closely with users’ needs [84,87]. Indeed, usability tests with 3 patients with SMI who were not involved in the design workshops showed that patients had a high level of satisfaction and intention to use SCIPP. Interventions are expected to benefit from this improved fit in multiple ways, including increased effectiveness [87], adherence [88,89], and adoption. Therefore, we expect that the mobile SCT app will provide an effective and suitable way to train self-control in the population with SMI. This should not be considered a stand-alone psychological treatment, but following this trial, the app could be implemented alongside any intervention aimed at improving the lifestyle of people with SMI to bolster its effectiveness.

To examine SCIPP in concert with Google Fit, we will use 2 SCEDs. The classic RCT is—despite its shortcomings—still the most dominant design for eHealth evaluation [41]. However, assembling the homogeneous population that is required for controlled trials is difficult or even impossible to achieve because of the relatively high number of patients with comorbidities. The fact that people with SMI are considered difficult to involve in larger trials such as RCTs may explain the lack of studies on their physical activity levels. This illustrates a paradox: even though vulnerable populations require more research to improve care, they are very hard to involve in classic study designs, which results in an underrepresentation in scientific literature, which in turn further aggravates inequalities [90]. SCEDs provide a good method to address this paradox as they allow for high-quality experimental research by intensively monitoring a limited number of patients. The first studies show that SCEDs are very suitable for the evaluation of eHealth interventions [41,42] and offer an excellent and feasible alternative to more classic experimental designs such as the RCT. However, although SCEDs appear to be a fitting research design, they have not been used to study eHealth physical activity interventions developed for people with SMI. This implies the need for more studies that apply SCEDs. Consequently, this project will apply 2 SCEDs to evaluate the effectiveness of combining a cognitive-based physical activity intervention with a mobile app to train self-control. This study will also explore people with SMI’s experiences of being involved in such an extensive longitudinal study. As such, these findings will also allow other researchers to learn the benefits and pitfalls of applying this relatively novel design to the evaluation of other eHealth interventions.

### Strengths and Limitations

A major strength of this study is the combination of 2 approaches to SCED: the multiple-baseline design across participants and the introduction/withdrawal design. The first experiment will allow us to demonstrate whether mobile SCT is effective, for whom it may be most effective, and for how long it should be offered for optimal effects. In addition, the qualitative interviews provide insights into how to optimize the mobile SCT app as well as insights into participation in an extensive longitudinal study from the perspective of people with SMI. This knowledge will be directly applied to the second experiment, in which the optimized intervention will be offered to a new set of patients to validate these findings.

Second, the study also uses accelerometry to assess the physical activity of people with SMI objectively. The use of accelerometry data substantially improves the reliability, validity, and level of detail of data on sedentary behavior and physical activity compared with often-used self-reports in which physical activity levels are consistently overestimated [91-93].

The main limitation is that there is no certainty that people with SMI will persist in SCT, faithfully wear the accelerometer, and provide answers to the daily questionnaires for the considerable study duration of 7 weeks. Nonadherence is a major challenge for any longitudinal study, including N-of-1 designs such as SCED [94]. However, it is specifically challenging in people with SMI [95], and studies suggest that low self-control may also further contribute to low adherence [96]. As this study is both longitudinal and will target individuals with SMI (who commonly have lower self-control than the general population [97]), nonadherence may thus be expected. To address this limitation, we will take additional measurements to avoid complete loss of data (eg, 2 daily measures of self-control instead of 1), schedule regular phone calls and visits by the researcher, and offer financial incentives for continued participation in the study, all strategies associated with better adherence [98-100]. Explicitly reporting on the success of these strategies both from a quantitative (eg, use data) and qualitative (eg, patient interviews) perspective will also help other researchers make more informed decisions about the design of SCED studies specifically in the population with SMI.

